Under the controversial debate over whether universal or selective hip screening is better [11,12], universal screening was strongly recommended in an international consensus paper [13]. In Japan, more than 90% of local governments conduct maternal and child health services [14], presenting a good opportunity for universal hip screening in communities. Newborn and infant home visits are a crucial healthcare strategy for supporting maternal and child health in each community [15]. Public health nurses and midwives have been conducting home visits for newborns and infants since the 1960s [16]. When the use of traditional Japanese-style diapers and baby clothing contributed to DDH as they extended infants’ legs, medical doctors and nurses educated caregivers on how to recommend a new diaper style that maintains the natural flex position of infants’ legs during home visits [17,18]. With the success of this health education program, the incidence of DDH in Japan has significantly decreased and now stands at approximately 0.1% [19]. However, despite home visits and infant health checkups being conducted, a nationwide survey revealed that approximately 15% of DDH cases were diagnosed after the child turned one year old [20]. The national government emphasized the necessity of finding DDH cases in each community [21]. 

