### 2.2. Participants

Participants will be recruited using snowball sampling. We will recruit approximately 30–40 nurses to consider the feasibility and limited budget. The inclusion criteria are that participants must be public health nurses, midwives, or registered nurses (any license is acceptable) who have conducted newborn and infant home visits. The exclusion criteria are individuals who are health volunteers for infant home visits and do not have a nursing license. 

Participant demographic data will be collected at study registration, including age, sex, job title, department, license, years of public health experience, years working in maternal and child health, and years of clinical experience in a hospital setting.

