Participants (nurses) will take the e-learning course after study registration, followed by an on-site hands-on seminar. The 105 min hands-on seminar comprises a lecture and practical training using phantoms. The phantom reproduces the normal hip joint. After training with the phantom, skills are evaluated by Objective Structured Clinical Examination (OSCE). Participants who pass the OSCE can proceed to the next step.

Finally, clinical training will be provided. The hip joints of infant volunteers within approximately four months, recruited by opportunity, will be examined. The first half of the clinical training will assess infants with physician supervision and guidance. In the second half of the training, participants will independently assess another infant without supervision. 

The ultrasound device *iViz air Ver.5 linear* (Fujifilm, Tokyo, Japan) will be used in all the training and examinations to standardize the procedures and readings. This device weighs 197 g, is easy to carry, and has been introduced to many home visiting nurses in Japan [31].

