### 2.4. Instruments and Measures

#### 2.4.1. E-Learning

Knowledge tests on the content of each module will be incorporated for knowledge retention and evaluation. The test will evaluate the participant’s ability to distinguish normal/abnormal ultrasound images.

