### 2.5. Statistical Analysis

Knowledge test results, OSCE scores, success rates of standard plane imaging, and time required for imaging will be reported using descriptive statistics. Inter-rater reliability will be reported using the prevalence adjusted bias adjusted kappa for each participant. The sensitivity and specificity of manual examination nurse and ultrasound examination by a nurse will be compared, with the diagnostic results from a physician as the gold standard.

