## Figures and Tables

**Figure 1 nursrep-14-00012-f001:**
[figure not shown]
Schematic models of the community-based ultrasound hip screening system for preventing overlooked DDH cases in newborn and infant home visits [30]. Note: The area bounded by the dotted line is the current study. The reference number in the caption for the publication in the image was [33] ([name], & [name], 2021).

**Table 1 nursrep-14-00012-t001:** Table of contents of the education and training program.

	Contents	Time (Minutes)	Materials/Subjects	Evaluation Measurement
1	E-learning:			
	∙ Ultrasound basics	25	RINGNE	∙ Knowledge test for each module
	∙ Anatomy of the hip joint	15	Original ([name], [name])	
	∙ Principles of the Graf method and ultrasound image reading	15	Original ([name], [name])	
	∙ Practice of the Graf method	10	Original ([name], [name])	
	∙ Ultrasound practice and health education in the newborn home visits	25	Original ([name], [name], [name])	
2	Hands-on seminar			∙ OSCE (operation of ultrasound equipment, technical proficiency)
	∙ Lecture	45	Original ([name], [name], [name])	
	∙ Practical training using phantom	60	Phantom (Kyoto Kagaku Co., Ltd., Kyoto, Japan)	
3	Clinical training			∙ Success rate of imaging ∙ Time required for imaging ∙ Assessment results from manual examination by a nurse; results from ultrasound examination by a nurse; and diagnostic results from a physician
	∙ Medical-supervised examination	30	Healthy volunteers within four months of age	
	∙ Unsupervised examination	90		

RINGNE: Research Institute for Next-Generation Nursing Education, OSCE: Objective Structured Clinical Examination. Time (minutes) for hands-on seminars and clinical training indicates training duration per participant in case of five participants per session.

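### The planned sensitivity comparison rests on healthy volunteer infants with no DDH cases added, so sensitivity will most likely be undefined and at best very imprecise

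*Protocol article*

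**What the plan says.** Section 2.5 commits to a specific accuracy analysis: "The sensitivity and specificity of manual examination nurse and ultrasound examination by a nurse will be compared". The reference standard for both methods is what the physician diagnoses. The data are collected in clinical training (section 2.4.3), where the nurse's manual result, the nurse's ultrasound result and the physician's diagnosis are recorded.

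The infants are described twice. Section 2.3 says: "The hip joints of infant volunteers within approximately four months, recruited by opportunity, will be examined". Table 1 lists the clinical-training subjects as "Healthy volunteers within four months of age". Neither place provides for known DDH cases.

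On size, section 2.2 says: "We will recruit approximately 30–40 nurses to consider the feasibility and limited budget". The number of infants is not given; section 2.3 has each nurse assess one other infant in the unsupervised half. On frequency, the Introduction says that incidence in Japan "now stands at approximately 0.1" per cent and gives about 1.4% prevalence from a literature review.

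The only planned contact with abnormal findings is the e-learning knowledge test, which assesses the "ability to distinguish normal/abnormal ultrasound images" (section 2.4.1).

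**The concern.** A missed case is a failure of sensitivity, and sensitivity has physician-positive infants as its denominator. A sample of healthy infants at these frequencies supplies almost none. This follows from who is examined, so an analysis plan could not repair it.

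Two things are at stake. First, a stated comparison will probably return 0/0 for both methods. Second, the accuracy figures that remain can look favourable without showing any ability to recognise an abnormal hip. If all hips are normal, a nurse who calls every hip normal has 100% specificity and perfect agreement with the physician. The article's Conclusions section speaks of evidence for accurate assessment and of missed and late detection, so readers could take such figures as support for detection.

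**Working it through.** The article gives no figure for expected cases or precision, so there is none to reproduce.

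**Inputs**
- Nurses: 30–40 (section 2.2).
- DDH frequency p: 0.1% for Japan and 1.4% from the review (Introduction), applied per infant as the rate of physician-positive results. This is an assumption.
- Infants n: not stated. Assumed values are 30–40 (one distinct unsupervised infant per nurse), 160 (40 nurses × 4 infants, a generous case) and 8 (one infant shared by each session of five nurses, 40 / 5).

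**Expected cases and chance of none.** Expected cases = n × p; chance of none = (1 − p)^n.

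| n | Expected, p = 0.1% | Chance of none | Expected, p = 1.4% | Chance of none |
|---|---|---|---|---|
| 8 | 0.008 | 99.2% | 0.112 | 89.3% |
| 30 | 0.03 | 97.0% | 0.42 | 65.5% |
| 40 | 0.04 | 96.1% | 0.56 | 56.9% |
| 80 | 0.08 | 92.3% | 1.12 | 32.4% |
| 160 | 0.16 | 85.2% | 2.24 | 10.5% |

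Selecting healthy infants would push the expected counts lower still.

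**Precision if cases do occur.** If all k of k cases are detected, the exact (Clopper–Pearson) 95% lower limit is 0.025^(1/k), with an upper limit of 100%:
- k = 1: 2.5%
- k = 2: 15.8%
- k = 5: 47.8%
- k = 10: 69.2%

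Even with 160 infants at 1.4%, the chance of five or more cases is only 7.6%.

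**Comparing the two methods.** Both methods are applied to the same infants, so the comparison is paired. The article names no test; the exact McNemar test serves as a yardstick. With d discordant cases all in one direction, two-sided p = 2 × 0.5^d. Five give 0.0625 and six give 0.031, so at least six discordant DDH cases are needed for p < 0.05.

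**Unselected sample needed.** For a 95% chance of even one case, n = ln 0.05 / ln(1 − p), rounded up: 2,995 infants at 0.1% or 213 at 1.4%. To expect ten cases, n = 10 / p: 10,000 or 715 infants.

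**What remains estimable.** Specificity does. If all of n normal infants were called normal, the exact 95% lower limit would be 0.025^(1/n): 88.4% for n = 30 and 91.2% for n = 40, treating infants as independent. The prevalence-adjusted bias-adjusted kappa is 2 × (observed agreement) − 1. A nurse who calls every hip normal, when all are normal, has observed agreement 1 and so a kappa of 2 × 1 − 1 = 1.

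**The case against.** **The main result does not depend on this.** This stands. The primary outcome is imaging success in the unsupervised examination (section 2.4.3), which needs no DDH case. Sensitivity and specificity are not among the secondary outcomes listed in the abstract, and no sample size rests on them. A reader might infer that the study as a whole is undermined; the documents do not support that.

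**The number of infants may be larger.** This stands as a caution. One infant per nurse is an assumption. A per-nurse kappa and a success rate running from 0 to 100% fit better with several infants per nurse, and supervised examinations may also count. But 160 infants still give an 85.2% chance of no case at 0.1% and only about two expected cases at 1.4%.

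**A positive result is not defined.** The article also speaks of suspicious cases, so the physician-positive rate could exceed the DDH frequency. This stands in part. However, merely to expect six positives would take a rate of 6 / 40 = 15% with 40 infants or 6 / 160 = 3.75% with 160. All six would then have to be discordant in the same direction.

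**The DDH-detection aim does have data behind it.** A reader might infer that it has none. That goes too far: the knowledge test includes abnormal images, and specificity and agreement on normal hips remain estimable. None of these, though, shows detection of DDH in infants.

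**Weak supporting points.** "The phantom reproduces the normal hip joint", but the phantom belongs to the seminar and contributes nothing to this comparison. Nor does the article give a nurse false-positive rate, so no particular specificity can be predicted. In Table 1 the healthy-volunteer entry sits on the supervised row and the unsupervised cell is blank, probably a merged cell. Section 2.3 describes volunteers for clinical training as a whole.

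**Conclusion.** The point holds for the sensitivity comparison in section 2.5. At the article's own 0.1%, sensitivity will most likely be undefined: the chance of no case is 96–97% with 30–40 infants and 85% with 160. At 1.4% with 30–40 infants, no case is still the likelier outcome (57–66%). At 1.4% with 160 infants some case is likely, but about two are expected, too few for a useful estimate or comparison. It would therefore be wrong to say that sensitivity certainly cannot be estimated; the accurate statement is that it will probably be undefined and at best not estimable with useful precision.

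The conclusion rests on the assumed infant numbers, on equating physician-positive results with the quoted DDH frequencies, and on no known cases being added. It concerns one stated additional analysis and the accuracy conclusions drawn from it. The primary outcome is unaffected.

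**What to change.** In section 2.5:
- Remove the sensitivity comparison from the infant examinations. If a case occurs, report it as a raw count only.
- Compare manual examination and ultrasound on specificity (false-positive rate), with a 95% CI.
- Report image-reading sensitivity and specificity separately, from the normal and abnormal knowledge-test images, using images with a known diagnosis. State that this measures reading only. It covers neither manual examination nor scans that the nurses acquire, so it does not replace the manual-versus-ultrasound comparison.

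In the Conclusions, state that the accuracy evidence is limited to plane acquisition, image reading and specificity in healthy infants, and does not extend to detection of DDH in infants. Specificity and the kappa should be presented with the note that calling every hip normal would score perfectly on both when all hips are normal.

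The cost is rewording and use of test images already planned, with no added infants. The downside is a narrower accuracy claim.

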### 2.6. Ethical Considerations

This study will be conducted following the Declaration of Helsinki. Ethical approval was obtained from the primary investigator’s ethics review committee (Research Ethics Committee of the Faculty of Medicine of the University of Tokyo, no. 2023101NI). To protect participants’ privacy, the authors will explain the study aim and procedures. Only participants who provide informed consent, whether by themselves or their surrogate, can participate in this study. To protect participants’ privacy, we will use pseudonyms throughout the study.

## 3. Conclusions

The nursing educational program, which focuses on ultrasound hip screening, will help improve nurses’ assessment skills and knowledge of suspicious DDH cases in newborns and infants during home visits. The current findings will provide crucial evidence to support the nursing profession in conducting ultrasound hip screening and in promoting accurate assessments during community-based newborns and infants home visit. The educational program addresses the issue of missed and late detection of DDH cases in resource-limited communities. This study will demonstrate the feasibility of procedures and the effectiveness of the educational program in 2024. 

## Figures and Tables

**Figure 1 nursrep-14-00012-f001:**
[figure not shown]
Schematic models of the community-based ultrasound hip screening system for preventing overlooked DDH cases in newborn and infant home visits [30]. Note: The area bounded by the dotted line is the current study. The reference number in the caption for the publication in the image was [33] ([name], & [name], 2021).

**Table 1 nursrep-14-00012-t001:** Table of contents of the education and training program.

	Contents	Time (Minutes)	Materials/Subjects	Evaluation Measurement
1	E-learning:			
	∙ Ultrasound basics	25	RINGNE	∙ Knowledge test for each module
	∙ Anatomy of the hip joint	15	Original ([name], [name])	
	∙ Principles of the Graf method and ultrasound image reading	15	Original ([name], [name])	
	∙ Practice of the Graf method	10	Original ([name], [name])	
	∙ Ultrasound practice and health education in the newborn home visits	25	Original ([name], [name], [name])	
2	Hands-on seminar			∙ OSCE (operation of ultrasound equipment, technical proficiency)
	∙ Lecture	45	Original ([name], [name], [name])	
	∙ Practical training using phantom	60	Phantom (Kyoto Kagaku Co., Ltd., Kyoto, Japan)	
3	Clinical training			∙ Success rate of imaging ∙ Time required for imaging ∙ Assessment results from manual examination by a nurse; results from ultrasound examination by a nurse; and diagnostic results from a physician
	∙ Medical-supervised examination	30	Healthy volunteers within four months of age	
	∙ Unsupervised examination	90		

RINGNE: Research Institute for Next-Generation Nursing Education, OSCE: Objective Structured Clinical Examination. Time (minutes) for hands-on seminars and clinical training indicates training duration per participant in case of five participants per session.

## Data Availability

Not applicable.
